**Methods:**

This is a prospective, multicenter, cluster-randomized controlled trial conducted across emergency medical services (EMS) in the regions of Gütersloh, Minden-Lübbecke, and Osnabrück. Adult patients (≥ 18 years) with OHCA who are undergoing mechanical ventilation through an airway device will be enrolled. The clusters (regional districts) will be randomized into two groups: one group will receive ventilation with PEEP set at 5 mbar (intervention group), while the other group will receive ventilation with ZEEP (control group). The study’s primary endpoint is the occurence of ROSC. Secondary endpoints include occurence of re-arrest, death during pre-hospital care phase, hospital admission during ongoing resuscitation, hospital admission with spontaneous circulation, peripheral oxygen saturation, and endtidal CO_2_ at hospital admission.

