### Relevant concomitant care permitted or prohibited during the trial {11d}

All standard resuscitation measures according to current European Resuscitation Council (ERC) guidelines are permitted, including chest compressions, defibrillation, and administration of emergency medications (e.g., epinephrine, amiodarone, lidocaine).

After ROSC, ventilation management will follow standardized targets across both study groups to ensure consistency during the post-resuscitation phase:FiO₂ titration to maintain peripheral oxygen saturation (SpO₂) above 94%End-tidal CO₂ (ETCO₂) between 35 and 45 mmHgTidal volume of 6–8 mL/kg predicted body weight

The PEEP level will remain consistent with the group allocation throughout the post-ROSC phase—5 mbar in the intervention group and 0 mbar (ZEEP) in the control group—as documented in the eCRF.

This approach ensures uniform post-ROSC ventilation management while maintaining the integrity of the randomized intervention. All parameters are automatically recorded and subsequently extracted from the ventilator and eCRF for analysis.

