### Provisions for post-trial care {30}

The study concludes upon the patient’s admission to the hospital.

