### Sample size {14}

The planned sample size is approximately 600 out-of-hospital cardiac arrest (OHCA) cases, with about 300 patients per group (PEEP vs. ZEEP).

The PerAVent trial is designed as a pilot and feasibility study, primarily aimed at evaluating the practical implementation of PEEP versus ZEEP ventilation in the pre-hospital setting and generating preliminary data for future confirmatory research.

The study hypothesis is that ventilation with PEEP (5 mbar) increases the probability of return of spontaneous circulation (ROSC) compared with ZEEP (0 mbar).

As this is a pilot study, no formal sample size calculation or power analysis has been performed, since no reliable prior data exist on which to base such assumptions. The chosen sample size is therefore based on feasibility considerations and expected case numbers within the participating emergency medical service regions over the planned study period.

The collected data will serve to estimate key parameters—such as recruitment rates, adherence, and effect size estimates—that may inform the design of a future confirmatory trial.

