## Data collection and management

### Plans for assessment and collection of outcomes {18a}

Data acquisition will be carried out using an eCRF, which is to be completed by the emergency care team following the resuscitation. The data collected will be supplemented with the ventilation parameters recorded by the emergency ventilators. The variables collected in the eCRF are shown in Table 1.

**Table 1 Tab1:** Variables collected in the eCRF

Category	Collected variables
Patient factors	Age (years), Sex, Comorbidities
Airway factors	Bag-mask ventilation before airway device placement (yes/no), Intubation (extraglottic airway device vs. endotracheal tube), Type of extraglottic airway device, Number of insertion attempts, Complications during insertion, Number of intubation attempts, Complications during intubation, Abandonment of intubation attempts, Re-intubation by emergency physician
Resuscitation data	Observed cardiac arrest (yes/no), Cardiac arrest observed by (layperson/emergency services), Layperson CPR performed (yes/no), Time to initiation of chest compressions, Resuscitation duration (minutes), Initial ECG findings, Defibrillation (yes/no), Number of defibrillations, Type of chest compressions (manual vs. mechanical), Type of mechanical compression device, Administration and cumulative dose of epinephrine and amiodarone
Intra-arrest ventilation data	Ventilation parameters set by emergency services (Pmax, PEEP, respiratory rate, tidal volume, inspiration-expiration ratio, FiO_2_, Ventilation mode: IPPV, BILevel, CCSV, Other), Ventilation parameters measured by Medumat Transport, Changes in ventilation parameters during resuscitation
Post-arrest treatment	Re-intubation from extraglottic airway to endotracheal tube (yes/no), Number of intubation attempts, Type and dose of analgesic, hypnotic, muscle relaxant, Complications in pre-hospital post-arrest phase (aspiration, ventilation issues, hypotension, re-arrest), Administration of catecholamines, Post-arrest ventilation settings
Additional outcome data	Consciousness at handover, ECG findings at handover, Glasgow Coma Scale, Vital parameters at handover (systolic blood pressure, heart rate, oxygen saturation, respiratory rate, etCO_2_), Initial blood gas analysis, Date of death, Hospital discharge date

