## Statistical methods

### Statistical methods for primary and secondary outcomes {20a}

For the primary outcome (ROSC), a mixed logistic regression model will be used to analyze the difference in the probability of achieving ROSC between the two groups (PEEP vs. ZEEP). This model will account for the cluster-randomized design, adjusting for potential correlations within clusters (EMS regions).

For secondary outcomes, such as re-arrest rate, death during pre-hospital care, hospital admission during ongoing resuscitation, hospital admission with spontaneous circulation, SpO₂, FiO₂, and etCO₂ at hospital admission, linear regression models will be used for continuous variables, while logistic regression will be applied for binary outcomes (e.g., shockable vs. non-shockable rhythms).

The models will include relevant covariates, such as age, comorbidities, and other baseline characteristics, to adjust for potential confounders. Random effects will be included to account for variability between EMS regions.

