### Additional statistical considerations

All analyses will be conducted on an intention-to-treat basis. Exploratory subgroup analyses are planned to evaluate potential effect modifications, including presumed etiology of OHCA (respiratory/asphyxial vs. primary cardiac) and airway management difficulty. These analyses will be hypothesis-generating and interpreted with caution.

The study hypothesis is that ventilation with PEEP (5 mbar) increases the probability of ROSC compared with ZEEP (0 mbar).

No interim analyses are planned.

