### Methods in analysis to handle protocol non-adherence and any statistical methods to handle missing data {20c}

Missing or incomplete data will be monitored continuously through automated completeness checks within the eCRF. In cases of protocol non-adherence or deviations in data entry, the coordinating center will contact the respective EMS team for clarification and data verification.

All missing data and deviations from the protocol will be documented and reported transparently.

For the statistical analysis, missing data will be handled using appropriate methods depending on the type and extent of missingness. If feasible, multiple imputation will be applied for missing covariate data. Sensitivity analyses will be conducted to evaluate the robustness of the primary results under different assumptions regarding missingness and protocol adherence.

This approach ensures transparency, minimizes potential bias, and maintains the methodological rigor of the study despite the operational challenges of data collection in the pre-hospital setting.

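### Re-arrest and admission SpO2, FiO2 and etCO2 exist only after ROSC or admission, which PEEP is hypothesised to change, so their planned arm comparisons are not intention-to-treat

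*Protocol article*

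**What the plan says.** Statistical methods {20a} names re-arrest, pre-hospital death, the two hospital-admission outcomes, and SpO2, FiO2 and etCO2 at admission, and states that "linear regression models will be used for continuous variables, while logistic regression will be applied for binary outcomes". Additional statistical considerations adds: "All analyses will be conducted on an intention-to-treat basis".

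Other sections show for whom these outcomes exist:

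- Table 1, in {18a}, records re-arrest under post-arrest treatment: "Complications in pre-hospital post-arrest phase (aspiration, ventilation issues, hypotension, re-arrest". A patient without ROSC has no post-arrest phase.
- The abstract and Outcomes {12} list "death during pre-hospital care phase" as a secondary endpoint, so the plan expects some patients never to reach admission.
- Outcomes {12} places time to discharge among the other outcomes and limits it to survivors.
- For missing data, {20c} names a method for covariates only: "If feasible, multiple imputation will be applied for missing covariate data".

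The hypothesis in Sample size {14} is that "ventilation with PEEP (5 mbar) increases the probability of return of spontaneous circulation (ROSC) compared with ZEEP (0 mbar".

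Concomitant care {11d} sets post-ROSC targets for both arms: "FiO₂ titration to maintain peripheral oxygen saturation (SpO₂) above 94" per cent, and etCO2 between 35 and 45 mmHg.

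**The concern.** Randomisation protects a comparison only when every randomised patient contributes an outcome. Here, whether a patient has a re-arrest status or an admission value depends on ROSC or admission, which follow randomisation and which PEEP is hypothesised to influence. Under the trial's own hypothesis, the PEEP arm contains ROSC patients whose counterparts under ZEEP had no ROSC. If those added patients are more fragile, the PEEP subset looks worse on re-arrest and on admission SpO2 even though PEEP made no individual worse.

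This matters in a pilot. Re-arrest is a natural harm signal in a trial that asks whether PEEP helps without adverse haemodynamic effects, and {14} says the effect estimates may inform a confirmatory trial.

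The gas values have a second difficulty. After ROSC they are managed towards targets, and patients admitted under ongoing CPR fall outside those targets. A pooled mean mixes the two states.

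**Working it through.** The plan gives no figure to reproduce: {14} states that no power calculation was made. The inputs are therefore the planned 300 per group, the background proportions in the Introduction, and assumptions labelled as such.

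**How many patients have the outcome.** The Introduction puts usual ROSC at 30% or less, cites one study at about 50%, and gives survival to discharge of 8 to 18%.

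- ROSC: 300 × 0.30 = 90 to 300 × 0.50 = 150 per group, so about 50 to 70% of a group would have no re-arrest status.
- Discharged alive: 300 × 0.08 = 24 to 300 × 0.18 = 54 per group, so 82 to 92% would have no discharge time.

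**Size of the re-arrest artefact.** Assumptions: ROSC is 30% under ZEEP and 35% under PEEP; PEEP never prevents ROSC; patients who would have ROSC under either arm re-arrest at 20% whichever arm they are in; added ROSC patients re-arrest at r. The added share of PEEP ROSC patients is 5/35 = 14.3%. Re-arrest among PEEP ROSC patients is (30 × 0.20 + 5 × r)/35, against 20% under ZEEP.

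| r | PEEP, among ROSC | Apparent excess | ROSC without re-arrest, all enrolled (PEEP vs ZEEP) |
|---|---|---|---|
| 20% | 7.0/35 = 20.0% | 0 | 28.0% vs 24.0% |
| 30% | 7.5/35 = 21.4% | 1.4 points | 27.5% vs 24.0% |
| 40% | 8.0/35 = 22.9% | 2.9 points | 27.0% vs 24.0% |
| 50% | 8.5/35 = 24.3% | 4.3 points | 26.5% vs 24.0% |

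The last column is ROSC minus re-arrest over all enrolled patients, for example 35 − 8.5 = 26.5 and 30 − 6 = 24. It favours PEEP throughout, as it should when PEEP only adds ROSC.

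Counting patients without ROSC as having no re-arrest does not help. At r = 50% this gives 8.5% against 6.0% of all enrolled, and at r = 20% still 7.0% against 6.0%, because more patients are at risk.

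**Against sampling noise.** With 105 and 90 ROSC patients, the standard error of the 4.3-point difference is √(0.243 × 0.757/105 + 0.20 × 0.80/90) = 5.9 points, so z = 4.3/5.9 = 0.7, ignoring clustering.

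**A stronger assumed case.** ROSC 40% against 30%, with re-arrest 60% in added patients and 30% in the others: (0.30 × 0.30 + 0.10 × 0.60)/0.40 = 37.5% against 30.0%, odds ratio (0.375/0.625)/(0.30/0.70) = 1.40. In 20,000 simulated trials of 300 per arm without clustering, 21% gave p < 0.05 with no individual effect on re-arrest. ROSC without re-arrest over all enrolled was 25.0% against 21.0%.

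**Admission SpO2, selection.** The shift is (added share) × (difference in mean of added patients). If added patients are 2 to 4 points lower, ROSC of 35% against 30% gives 5/35 × (−2) = −0.3 to 5/35 × (−4) = −0.6; ROSC of 50% against 30% gives 20/50 × (−4) = −1.6.

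**Admission SpO2, targets.** A simulation assumed a true 2-point gain, baseline mean 93, SD 5, a ceiling of 100, and FiO2 titration lifting values below 95 to 95. The observed difference was 1.8 points with no titration, 0.8 if 80% reach target and 0.6 if all do.

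**The case against.** The strongest reply is that the denominator is unstated rather than wrongly fixed. Section {20a} does not restrict re-arrest to ROSC patients, intention-to-treat may only mean analysis by allocated arm, and a condensed article may leave analysis sets to an SAP that is not shown. Part of this stands: the article prescribes no survivors-only analysis. But it does fix the models and a blanket label, and neither reading of the denominator for re-arrest gives a clean comparison, as the working shows. Analysis by allocated arm does not restore comparability within a selected subset.

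Several stronger readings are tempting and are not supported:

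- That all these outcomes belong to survivors or ROSC patients. Outcomes {12} includes admission during ongoing resuscitation, so admission values can exist without ROSC.
- That time to discharge is one of the planned regressions. It has the same selection problem, but it is an other outcome outside the regression sentence in {20a}; only the general intention-to-treat statement reaches it.
- That SpO2 cannot show an oxygenation gain, or that the gain is hidden. The SpO2 target is a floor that applies after ROSC, the simulated difference was reduced rather than removed, and FiO2 at admission is itself a planned outcome.
- That re-arrest results will mislead by 4 points or more. That figure is the top of one assumed range, below one standard error at this size.

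It is also fair that re-arrest is a recorded complication and should not disappear from the report.

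**Conclusion.** The point holds in a limited form. Re-arrest and the admission values of SpO2, FiO2 and etCO2 are conditional on events that PEEP is hypothesised to change, and regression under an intention-to-treat label does not make the arms comparable. The apparent excess of re-arrest is 0 to 4.3 points with ROSC of 35% against 30% and larger under stronger assumptions. It is zero if PEEP does not change ROSC or if the added patients have equal prognosis. The re-arrest and ROSC-effect inputs are assumptions; the documents give none. SpO2 differences are additionally attenuated by the post-ROSC targets, and pooled etCO2 mixes patients with spontaneous circulation and patients under CPR.

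The primary outcome, pre-hospital death and the two admission outcomes are defined for every enrolled patient and are unaffected. This is a change that should be made to secondary outcomes of a pilot; it does not threaten the main result.

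A separate inconsistency sits nearby. Post-trial care {30} says "The study concludes upon the patient’s admission to the hospital", while Outcomes {12} lists Cerebral Performance Category (CPC) at discharge, and the assessment and visit sections describe in-hospital data collection. Table 1 has death and discharge dates but no CPC field. A reader might infer that no in-hospital data are planned; the assessment and visit sections say otherwise, so the passages need reconciling.

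**What to change.** 1. Add two yes/no outcomes with all enrolled patients as denominator and use them for the between-arm comparison: ROSC without re-arrest to hospital admission, and alive at discharge. The first differs from admission with spontaneous circulation, already an outcome, only where a re-arrest was followed by renewed ROSC.
2. Keep re-arrest among ROSC patients as a descriptive safety figure, with its denominator stated.
3. Report SpO2, FiO2, SpO2/FiO2 and etCO2 descriptively among admitted patients, separately for spontaneous circulation and ongoing CPR. SpO2/FiO2 remains conditional on admission.
4. Do not label these conditional comparisons intention-to-treat, and describe time to discharge as restricted to survivors.
5. Separately, reconcile {30} with {12} and the in-hospital assessment sections, and say how CPC is recorded or remove it.

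**Cost.** Items 1 to 4 are wording: ROSC, re-arrest, admission status, and death and discharge dates are already planned data. Table 1 lists no FiO2 among the handover parameters, so its source for the ratio should be named; post-arrest ventilation settings and ventilator read-outs are already collected. The downside is that the admission gas values become descriptive. Keeping CPC costs more than one field, because the emergency team completes the eCRF after the resuscitation whereas CPC must be obtained from the hospital, and recruitment is due to end on 31 May 2026.

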### Methods for additional analyses (e.g., subgroup analyses) {20b}

Exploratory subgroup analyses are planned to evaluate potential effect modifications related to the study intervention.

The presumed etiology of OHCA — categorized as respiratory/asphyxial versus primary cardiac — will serve as a key subgroup variable. This classification will be based on dispatcher information, scene findings, and the EMS team’s clinical impression.

In addition, the eCRF systematically records a broad range of parameters that allow for further exploratory analyses, including:Patient comorbidities (e.g., cardiac or pulmonary disease)Airway management characteristics (type of device, number of attempts, complications)Ventilation parameters (PEEP, FiO₂, etCO₂, SpO₂, pCO₂)

These variables will enable investigation of potential effect modifiers and interactions, such as which patient groups may particularly benefit from PEEP during resuscitation.

All subgroup analyses will be pre-specified, and interpreted with caution given the pilot nature of the study. The results will be considered hypothesis-generating to guide the design of future confirmatory research.

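### Delivered PEEP and post-allocation gas-exchange values are listed as possible effect modifiers of PEEP; separately, a rhythm that is not a listed outcome is given as the example of a binary outcome

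*Protocol article*

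**What the plan says.** All references are to the protocol article.

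- **Additional analyses {20b}.** Presumed aetiology is the key subgroup variable. The section then names further recorded parameters for exploratory work: comorbidities, airway management characteristics, and "Ventilation parameters (PEEP, FiO₂, etCO₂, SpO₂, pCO₂"). It continues: "These variables will enable investigation of potential effect modifiers and interactions", and gives as its example finding which patients benefit most from PEEP. It says the subgroup analyses will be pre-specified, read cautiously, and used to help design later confirmatory research.
- **Intervention description {11a}.** PEEP of 5 mbar or 0 mbar is the assigned treatment, set by the cluster randomisation.
- **Outcomes {12}.** SpO₂, FiO₂ and etCO₂ at hospital admission are secondary outcomes. No heart rhythm appears among the primary, secondary or other outcomes.
- **Statistical methods {20a}.** After naming the secondary outcomes, the section says "logistic regression will be applied for binary outcomes (e.g., shockable vs. non-shockable rhythms"). On adjustment it says "The models will include relevant covariates, such as age, comorbidities, and other baseline characteristics".
- **Table 1 {18a}.** Under resuscitation data the eCRF records "Initial ECG findings, Defibrillation (yes/no), Number of defibrillations". Under additional outcome data it records "ECG findings at handover".

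**The concern.** An effect modifier should be a characteristic that the treatment cannot have changed. Within levels of such a factor the randomised comparison survives; within levels of something measured after treatment began it need not. The ventilation list in {20b} contains the treatment itself, three measures that also serve as secondary outcomes, and one blood-gas value.

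At stake is what the pilot passes on. Its stated purpose is to inform a later trial. A subgroup finding based on delivered PEEP, SpO₂ or etCO₂ could suggest a target population that is only a product of conditioning on treatment or on outcome. Cautious interpretation does not remove that bias.

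The rhythm example is a smaller matter of consistency: the analysis section illustrates binary outcomes with a variable that the outcome section does not contain.

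**Working it through.** The protocol gives no power, effect size or event rate for these analyses, so it has no figure of its own to reproduce. The check has four parts.

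**1. When each listed variable is observed**

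| Variable | What the protocol shows | Consequence |
|---|---|---|
| PEEP | Assigned treatment {11a}; setting, measured value and changes recorded during resuscitation (Table 1) | It is the exposure, or adherence to it |
| SpO₂, etCO₂ | Monitored during resuscitation (Assessments); secondary outcomes at admission {12} | Can respond to PEEP and to ROSC |
| FiO₂ | Set during resuscitation (Table 1); titrated to SpO₂ after ROSC {11d}; secondary outcome at admission {12} | Can depend on ROSC and on SpO₂ |
| pCO₂ | The only listed source is the optional initial blood gas, scheduled between ROSC and handover (Assessments) | On that schedule, available essentially only in patients who already had the primary event |

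No value from before the assigned ventilation is defined for any of them. On that timing, a subgroup analysis of ROSC by pCO₂ would have almost no patients without ROSC in it.

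**2. Arm-by-PEEP interaction**

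Inputs: 300 patients per arm {14}; adherence levels are assumptions. Model columns: intercept, arm (1 or 0), delivered PEEP (5 or 0), arm × PEEP.

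- Full adherence: PEEP = 5 × arm and arm × PEEP = 5 × arm, so the last three columns are proportional. The matrix has rank 2 of 4, and the interaction cannot be estimated.
- 95% adherence: rank 4, but the off-protocol cells hold 300 × 0.05 = 15 patients per arm.
- 90% adherence: rank 4, with 300 × 0.10 = 30 per arm.

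Assume ROSC is 30% in every cell and ignore clustering. The standard error of the interaction, as a difference of risk differences, is √[0.3 × 0.7 × (2/n_on + 2/n_off)]:

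- 95%: √[0.21 × (2/285 + 2/15)] = √0.0295 = 0.172, or 17.2 percentage points.
- 90%: √[0.21 × (2/270 + 2/30)] = √0.0156 = 0.125, or 12.5 percentage points.

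The off-protocol cells are also selected, because {11b} lets the team change the setting on clinical judgement.

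**3. Splitting on a post-allocation variable when the true effect is zero**

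The inputs are assumptions, with 2,000,000 simulated patients per scenario. ROSC is about 30% and does not depend on arm. The post-allocation variable has a within-arm SD of about 1, rises with PEEP by the shift shown, and shares an unmeasured severity factor with ROSC. That factor acts on ROSC with the log-odds shown per SD. Patients are split at the median of the variable.

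| Shift (SD) | Log-odds | Overall difference (points) | Low half | High half |
|---|---|---|---|---|
| 0.25 | 0.5 | 0.0 | −1.0 | −1.2 |
| 0.25 | 1.0 | 0.0 | −1.7 | −2.4 |
| 0.5 | 0.5 | 0.0 | −2.2 | −2.4 |
| 0.5 | 1.0 | 0.0 | −3.7 | −4.7 |
| 1.0 | 0.5 | 0.0 | −4.3 | −4.8 |
| 1.0 | 1.0 | 0.0 | −7.2 | −9.5 |

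Both halves show an effect that does not exist, and the halves also differ from each other by 0.2 points (1.2 − 1.0) to 2.3 points (9.5 − 7.2). The sign follows from the assumed directions and could reverse under others.

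**4. The rhythm example**

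Table 1 has two ECG items. If the presenting rhythm is meant, it precedes the assigned ventilation, which starts once the airway is secured {13}, so it cannot be an outcome of PEEP. If the rhythm at handover is meant, it could be affected by PEEP, but {12} does not list it. Either way the example does not match the outcome list. Listed binary outcomes, such as "hospital admission with spontaneous circulation", stand in the same sentence of {20a}.

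**The case against.** The strongest reply is that {20b} promises little. It says the parameters make it possible to look for effect modifiers; it does not set out a test for each. The work is labelled exploratory, the key subgroup is aetiology, and the intention-to-treat analysis of ROSC does not use these variables. All of that stands, and it limits the consequence. It does not correct the roles: the variables are named for this purpose, the analyses are to be pre-specified, and their results are to shape the next trial.

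On rhythm, the sentence in {20a} is a parenthetical example and does not contain the word initial. A reader might infer that a baseline factor will be tested and reported as a result of treatment. The text does not support that, because no section sets out a rhythm endpoint and the handover ECG is a possible alternative meaning.

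A reader might also infer that initial rhythm is left out of the primary model. That is not shown either. The covariate list is open and other baseline characteristics may include rhythm; the exact list is commonly settled in the analysis plan, which is not at hand.

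**Conclusion.** The point holds for the exploratory effect-modifier analyses. Delivered PEEP cannot usefully modify its own effect: the interaction is not estimable with full adherence and rests on 15 to 30 selected patients per arm at 95% to 90% adherence. Subgrouping on FiO₂, SpO₂, etCO₂ or pCO₂ conditions on quantities that treatment or ROSC can change.

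The range of −1.0 to −9.5 points shows that spurious subgroup effects can arise. It rests entirely on the assumed shift and shared severity and does not forecast the bias in this trial.

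The primary analysis is not affected. The rhythm example is a minor mismatch with the outcome list. The protocol gives no ROSC rates by rhythm, so no bias in the primary result can be derived from it. The text should be corrected before the analysis, but nothing here threatens the main comparison.

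**What to change.** 1. In {20b}, limit effect-modifier analyses to factors fixed before the assigned ventilation starts, for example comorbidity, initial rhythm, witnessed status, presumed aetiology, and airway-management difficulty up to the first secured airway.
2. Take PEEP, FiO₂, etCO₂, SpO₂ and pCO₂ out of the effect-modifier list. Report delivered PEEP as adherence by arm, and the other four descriptively by arm with the time of measurement and the number of patients who have a value. The admission values of SpO₂, FiO₂ and etCO₂ stay as secondary outcomes.
3. In {20a}, replace the rhythm example with a listed binary outcome such as re-arrest.
4. In the same section, name initial rhythm among the baseline covariates, so that its role is clear.

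The cost is a wording change in the protocol and the matching text of the analysis plan. Table 1 already collects initial rhythm, witnessed status, comorbidities and the airway items, and {20b} already defines how aetiology is classified. No new data collection or change in sample size is needed.
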